**Figure 4 fig4:**
[figure not shown]
Strolll AR gait-and-balance exercises: Smash! [without **(A)** and with **(B)** assistive AR cues], Mole Patrolll **(C)**, Hot Buttons **(D)**, Basketballl **(E)**, Puzzle Walk **(F)**, Wobbly Waiter **(G)**, and Cue Challenge **(H)**.

Participants will be invited by their therapist to use Strolll AR minimally 5 times a week for 30 active minutes per day, resulting in the recommended 150 minutes per week (1, 7, 8). They can perform the exercises anytime during the day, in one bout or in multiple chunks during the day, with complementary AR cueing when deemed beneficial. The precise exercises, exercise duration, difficulty level, and order will be prescribed by the therapist via the Strolll web portal (Figure 5). Therapists were by default recommended to prescribe all AR exercises, as each AR exercise targets different aspects (see Supplementary material S2). However, they were allowed to make adjustments, if necessary, to align with the participant’s abilities and needs, as well as for practical considerations. The prescribed exercises will be evaluated and adjusted on a weekly basis in telephone calls, e-consults or during an onsite therapy session using information of the participant in combination with the feedback from exercises that are reported in the Strolll web portal, such as adherence and game-play and functional performance metrics (cf. Supplementary material S2). Adherence will be defined as the percentage of performed over prescribed gait-and-balance exercises [i.e., both frequency and session-duration adherence; (15)]. The data on game-play level and performance will be used to evaluate whether the exercise program was both progressive (increase in level) and achievable (consistently high game-play performance scores) as intended. The weekly contact moments with the therapist will also be used to ask if participants experienced any adverse events (safety flags). Specifically, safety will be evaluated as the number of adverse events due to the Strolll AR intervention, such as falls, dizziness, eye strain, and headache. Potential technical issues will be documented by the researcher, who will be available to provide technical support during the study based on email or telephone contact with the participants.

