#### Final assessment (T2): effectiveness and clinical feasibility

2.2.7

To be able to evaluate the effectiveness of the Strolll AR intervention, the therapist will again administer standard clinical tests of gait, balance, and falls risk (TUG, FTSTS, 10MWT, Mini-BESTest). Participants will fill out the FES-I questionnaire together with the researcher during a telephone call (Table 1).

Clinical feasibility of the Strolll AR platform according to the participants will be assessed in terms of user experience [i.e., the User Experience Questionnaire (UEQ); (37)], technology acceptance and use [i.e., questionnaire based on the Unified Theory of Acceptance and Use of Technology model (UTAUT; (38))], top-3 barriers and facilitators of Strolll AR, and intervention-specific questions regarding Strolll AR, including cueing if used during the intervention (see Supplementary material S3). Participants will also report their falls history during the intervention period. The questionnaires of the final assessment are completed through a telephone call with the participant to ensure comprehensibility, which was first assessed in think-aloud sessions with a number of participants (39). In light of the potential future implementation in the clinical pathway, therapists will also be asked about their experience with Strolll AR through a purpose-made questionnaire (see Supplementary material S4), including the technology acceptance and use questionnaire, the top-3 barriers and facilitators (assessed before training their first participants and after training their last participant), and the UEQ (assessed after their last participant completed the study). Furthermore, a focus group with the therapist will be organized after the study for an in-depth evaluation of the top-3 barriers and facilitators.

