### Discontinuation or modification of allocated intervention

2.5

Participants can leave the study at any time for any reason if they wish to do so without any consequences. The researcher can decide to withdraw a participant from the study for urgent medical reasons or when medication dosage is changed during the study. Participants that are withdrawn will not be replaced, because the sample-size calculation takes such dropouts into account. Reasons for drop out or withdrawal will be collected. Dropouts during the intervention period will be asked to complete the UEQ and Strolll AR evaluation questionnaire to reduce potential bias in the study’s participant experience results which could become manifest if only data from participants completing the intervention would be taken into account. For the other clinical tests and questionnaires, dropouts will lead to missing data.

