### Statistical analysis

2.7

Data analysis will be performed in JASP (42). Missing data will be excluded analysis-by-analysis.

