#### Feasibility (safety, adherence, performance, and user experience)

2.7.2

Clinical feasibility will be evaluated on several aspects. First, to determine if the Strolll AR intervention can be safely performed at home, descriptive outcomes will be reported for safety (i.e., number of dropouts during training at home including the reasons for withdrawal, adverse events including a paired-samples *t*-test comparison of the average weekly number of falls experienced during usual-care and intervention periods), providing insight into the potential risks of the Strolll AR intervention.

Second, to determine if the Strolll AR intervention was adherable over the course of the intervention, we will conduct a repeated-measures one-way ANOVA with the within-subject factor Time (three levels) on adherence scores derived from the first, second, and third part of the intervention at home (i.e., default intervention period is 6 weeks, so adherence is derived over roughly two-weeks intervals). The assumption of sphericity will be checked according to Girden (43). If Greenhouse–Geisser’s epsilon exceeds 0.75, the Huynh-Feldt correction will be applied; otherwise, the Greenhouse–Geisser correction will be used. Effect sizes will be quantified with *η*_p_^2^. Paired-samples *t*-tests will be used for post-hoc comparisons of a significant main effect of Time. In addition, one sample *t*-tests against 100% will be performed for adherence scores at each Time point to determine whether or not there were systematic deviations from the prescribed treatment.

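### The adherence ANOVA and the paired falls test leave out people who stop training at home, and the adherence score does not show the dose achieved against 150 minutes per week

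*Protocol article*

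**What the plan says.** All references are to the protocol article.

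- **Adherence test (section 2.7.2).** The home period is split into three parts and "we will conduct a repeated-measures one-way ANOVA with the within-subject factor Time (three levels) on adherence scores". One-sample t-tests "against 100% will be performed for adherence scores at each Time point" are added.
- **Falls test (section 2.7.2).** The safety report includes a paired-samples t-test for the "comparison of the average weekly number of falls experienced during usual-care and intervention periods".
- **Missing data (section 2.7).** "Missing data will be excluded analysis-by-analysis".
- **Dropouts (section 2.5).** People who drop out during the intervention are asked for the user experience and evaluation questionnaires. "For the other clinical tests and questionnaires, dropouts will lead to missing data".
- **Source of falls data.** Table 1 places the falls history at T1 and T2. On the final assessment, section 2.2.7 says: "Participants will also report their falls history during the intervention period". Usual-care falls come from a six-week recall at T1 (section 2.2.4).
- **Adherence score (section 2.2.6).** "Adherence will be defined as the percentage of performed over prescribed gait-and-balance exercises", for both frequency and session duration. "The prescribed exercises will be evaluated and adjusted on a weekly basis", using portal feedback that includes adherence itself. The same section sets a minimum of five 30-minute days, or 150 active minutes per week.
- **Contrast (section 2.7.2).** User experience is analysed in everyone who started in the clinic, expressly to avoid selecting completers.

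**The concern.** Feasibility, including safety and adherence, is named as a primary study parameter in the abstract. The ANOVA is meant to show whether people kept up the programme over the home period. Stopping altogether is the plainest failure to keep it up, yet a repeated-measures ANOVA uses only people with a score in all three parts. The paired falls test likewise needs a report from both periods, and a person who stops has no planned T2 report. Both tests are then conditioned on not stopping, which is closely tied to what they are meant to assess. The authors guard against this selection for user experience but do not say that they do so here.

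A second, separate issue is the denominator. If the prescription is lowered after poor adherence, the score rises although the person trains less. The planned figure then answers whether people did what was prescribed, but not how much they trained relative to the protocol's own target.

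**Working it through.** **The plan's own figure.** The only calculated figure is the TUG sample size in section 2.4; none is given for adherence or falls. With d = 2.57/3.4 = 0.756 (stated as 0.755), two-sided 5% and 80% power, the noncentral t gives 28.53, so 29 per group and 58 in total (power 0.807). It reproduces and is not affected by this point.

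**1. Who is left out.** Inputs are the expected losses in section 2.4: 100 enrolled, about 10 lost in usual care, about 10 in the in-clinic phase and about 10 at home.
- Home starters: 100 − 10 − 10 = 80
- Completers: 80 − 10 = 70
- Share of home starters missing from both tests: 10/80 = 12.5%

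**2. Adherence in the last part, upper bound on the gap.** Suppose all 10 stop before the last part and count as zero in it. Mean over all starters = (70 × A + 10 × 0)/80 = 0.875 × A, where A is the completer mean (assumed, since the document gives none).

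| Completers | All home starters | Gap (points) |
|---|---|---|
| 100% | 87.5% | 12.5 |
| 90% | 78.8% | 11.2 |
| 80% | 70.0% | 10.0 |
| 70% | 61.3% | 8.7 |

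**3. A milder case.** A simulation of 2,000 runs assumed 80 starters, adherence flat over time at about 84%, and 10 people stopping uniformly over the six weeks with zero afterwards.
- Completers only: 83.7 / 83.7 / 83.7%; Time effect significant in 6% of runs.
- All starters: 82.0 / 78.5 / 75.0%; Time effect significant in 88% of runs.

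The gap is 83.7 − 75.0 = 8.7 points in the last part. Over six weeks it is 83.7 − (82.0 + 78.5 + 75.0)/3 = 83.7 − 78.5 = 5.2 points. The simulated F test had no sphericity correction, so the plan's correction would lower the 88% somewhat.

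**4. Falls.** Let r be the assumed ratio of stoppers' to completers' weekly fall rate. Weighting each person equally, the all-starter rate is (70 + 10r)/80 times the completer rate, so the understatement is 1 − 80/(70 + 10r).
- r = 1: 1 − 80/80 = 0%
- r = 2: 1 − 80/90 = 11%
- r = 3: 1 − 80/100 = 20%
- r = 5: 1 − 80/120 = 33%

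Weighting by person-time would shrink these, because stoppers are observed for less time.

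**5. Denominator.** For someone who does everything prescribed, adherence is 100% at any prescription. Against 150 minutes, illustrative prescriptions of 120, 90 and 60 minutes give 120/150 = 80%, 90/150 = 60% and 60/150 = 40%.

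**The case against.** A reader might infer that people who stop vanish from the feasibility and safety results. The document does not support that. Section 2.7.2 reports home dropouts with their reasons, adverse events, and the fraction judged suitable for home use. Section 2.2.6 has adverse events, falls included, asked about at weekly contacts. Someone who stops because of a fall related to Strolll AR should therefore appear there. The one-sample tests are run part by part, so they can keep a stopper's early data, although they still lack that person once stopped.

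A reader might also infer that the portal records zero after stopping and that the plan discards those zeros. Nothing says so; had zeros been recorded, they would not be missing. The sentence in section 2.5 covers tests and questionnaires, not portal data, so exclusion from the ANOVA is the natural reading and not a stated rule. Section 2.7.2 calls six weeks the default and the intervals approximate, so the parts could be thirds of each person's own period. Stoppers would then be included, but only for time before they stopped, and a decline due to stopping would still not show.

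Two further limits stand. The gap of 10 to 11 points at completer means of 80 to 90% is a worst case for the last part only. The direction of any falls bias is not shown: it is nil if stoppers and completers fall equally often.

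On the denominator, performed over prescribed does answer the plan's question about departure from the prescription, and tailoring is part of the intervention. Prescriptions can also rise, because the target is a minimum. Minutes against 150 are thus a complementary measure and not a correction of an error.

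**Conclusion.** The point holds for the two tests named and not for feasibility and safety reporting as a whole. By the plan's own estimates, about 12.5% of home starters are absent from the paired falls test and, if adherence after stopping counts as missing, from the ANOVA. The ANOVA can then look flat while adherence over all starters declines. With completers at 90%, the last-part figure for all starters could be as low as 79%; with stopping spread evenly, the gap is about 9 points in the last part and about 5 overall. These sizes rest on assumed completer adherence and on counting time after stopping as zero. Falls are understated only if stoppers fall more often: by 11 to 20% at an assumed ratio of 2 to 3. Separately, the planned adherence score does not show the dose achieved against 150 minutes per week. This should be changed because feasibility is a primary aim and the changes are small.

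**What to change.** 1. **Adherence.** Add an analysis of everyone who starts at home, over the fixed six weeks, counting weeks after stopping training as zero. Handle withdrawals decided by the researcher (section 2.5 names urgent medical reasons and a changed medication dosage) separately, so that they are not scored as non-adherence. Keep the completer ANOVA as secondary. This is analysis wording; the price is a less favourable adherence figure.
2. **Dose.** Report active minutes per week against 150 beside performed-over-prescribed adherence. This is one further summary.
3. **Falls.** Ask the same falls-history question when someone stops; dropouts are already approached for two questionnaires at that point, so this adds one item. Compare periods as falls per person-week in all home starters, using a Poisson or negative binomial model with a person-time offset and within-person clustering. This uses incomplete periods and suits sparse counts in a sample whose eligibility criteria give frequent fallers as an example of people to exclude.
4. **Weekly safety contacts.** Report falls from these separately and do not feed them into the comparison. They are described only for the home phase, while usual care has a single six-week recall, so mixing the two would make ascertainment unequal.

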Third, the pre-cursor of Strolll AR, Reality DTx^®^, was found to be a progressive-but-achievable intervention in a research setting (15), where researchers balanced and tailored task demands and capacity (i.e., not too easy to prevent boredom and not too difficult to prevent demotivation) when remotely prescribing the exercises based on weekly telephone calls with the participants and their performance data from the Strolll web portal. To determine if Strolll AR, delivered in the clinical pathway, also results in a progressive-but-achievable intervention (i.e., increasing exercise levels over weeks while maintaining high-performance scores), levels and performance scores for each game were subjected to repeated-measures ANOVAs (or their non-parametric equivalent) with the factor Time (3 levels, first, middle, last part), using paired-samples *t*-tests (or their non-parametric equivalent) post-hoc analyses for significant effects of Time. We expect to find strong main effects of Time for exercise levels (with post-hoc effects showing an increase in exercise levels), but not or less so for performance scores.

Fourth, user experience will inform on acceptability among people with Parkinson’s disease and among therapists (i.e., top-3 barriers and facilitators questionnaire and an in-depth focus group) and usability (UEQ from both participants and therapists) of the Strolll AR intervention. To evaluate participant experience, all participants who started with the Strolll AR intervention in the clinic will be analyzed collectively (i.e., intention-to-treat protocol) to avoid a selection bias of the people who completed the intervention. The UEQ will not be analyzed statistically but will be reported as descriptive outcomes and interpreted against known benchmark scores (37). Also, other participants’ or therapists’ reported outcome measures from the questionnaires will be reported as descriptive outcomes. Finally, the fraction of participants deemed eligible for performing the intervention at home after having had the in-clinic Strolll AR sessions will inform about the usability of the intervention.

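### The Time ANOVA on game performance cannot show that scores are high, and a non-significant result does not show that they were maintained

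*Protocol article*

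**What the plan says.** Section 2.2.6 says that portal data on game level and performance will show whether the programme was "both progressive (increase in level) and achievable (consistently high game-play performance scores) as intended". Section 2.7.2 restates the criterion as "increasing exercise levels over weeks while maintaining high-performance scores". In both places achievable refers to the height of the score, and to its staying high.

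For the analysis, section 2.7.2 says that "levels and performance scores for each game were subjected to repeated-measures ANOVAs (or their non-parametric equivalent"), with Time (first, middle and last part) as the only factor and paired post-hoc comparisons where Time is significant. The expected pattern follows: "We expect to find strong main effects of Time for exercise levels", with post-hoc increases, "but not or less so for performance scores".

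The article gives no reference score, benchmark or decline margin for performance. Other outcomes in the same section do have a reference: adherence is tested against 100% at each time point as well as over Time, and the UEQ is read against known benchmark scores.

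On level, section 2.2.6 states: "The precise exercises, exercise duration, difficulty level, and order will be prescribed by the therapist via the Strolll web portal". The prescription is reviewed weekly, using portal feedback that includes performance metrics.

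**The concern.** The criterion is about where scores lie and whether they stay there. The named analysis asks only whether they change. That leaves two gaps.

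- **High.** A test of Time has no information on the height of the scores.
- **Maintained.** The supporting pattern for performance is a null or weaker effect. With no margin for decline, a non-significant result can mean stable performance or too few players to detect a fall.

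Performance is one of the four named components of feasibility, and the abstract lists feasibility among the primary study parameters. If the conclusion rests on the ANOVA pattern, achievable could be reported without evidence for either half of its definition. If it rests on inspecting the means, the value that counts as high would be chosen after the scores are known.

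**Working it through.** The article states no sample size, power, threshold or margin for this analysis, so there is no figure of its own to reproduce.

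**1. Height of the scores.** Let Y_ij be the score of participant i in part j. The Time F statistic is

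F = [n Σ_j (Ȳ_.j − Ȳ_..)² / (k − 1)] / [Σ_ij (Y_ij − Ȳ_i. − Ȳ_.j + Ȳ_..)² / ((k − 1)(n − 1))], with k = 3.

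Replace Y_ij by Y_ij + c. Every bracket is a difference of terms that each gain c, or a sum in which the c's cancel, so F does not change. The same holds for within-person ranks in a non-parametric version and for the paired post-hoc differences. No distributional assumption is needed.

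A simulation shows the same (20,000 runs per case; assumed 0–100 scale, SD 15, within-person correlation 0.6, alpha 0.05). The proportion of non-significant Time tests with flat means is:

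| Players per game | Mean 90 | Mean 60 | Mean 30 |
|---|---|---|---|
| 20 | 0.947 | 0.947 | 0.951 |
| 40 | 0.953 | 0.949 | 0.948 |
| 70 | 0.951 | 0.953 | 0.952 |

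**2. Maintained, first versus last part.** Assumptions: true fall 10 points, SD of the paired difference 25 points, two-sided 5%. Then d = 10/25 = 0.4, the noncentrality is d√n, and power comes from the noncentral t with n − 1 degrees of freedom.

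| Users of the game | d√n | Power | Fall missed |
|---|---|---|---|
| 15 | 1.55 | 0.30 | 70% |
| 50 | 2.83 | 0.79 | 21% |
| 70 | 3.35 | 0.91 | 9% |

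The 70 is the number of completers implied by section 2.4: 100 − 10 − 10 − 10 = 70. The 50 and 15 stand for games that therapists prescribe less often.

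**3. Maintained, three-part ANOVA.** Under the simulation assumptions in step 1, the SD of a paired difference is 15 × √(2 × 0.4) = 13.4. A steady fall from 90 to 85 gives a non-significant Time test in 72% of runs with 20 players, 47% with 40 and 20% with 70. A fall from 60 to 55 gives the same proportions, as step 1 requires.

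**4. Does a reference value separate the cases?** Take an assumed reference of 80 and test the last-part mean above it (SD 15, one-sided 0.025). A true mean of 90 is shown to exceed 80 in 81% of runs with 20 players, 98% with 40 and more than 99.9% with 70. True means of 60 and 30 are never shown to exceed it. The Time test treats all three means alike.

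**The case against.** The strongest reply is that the article states an expectation and sets no pass/fail rule. This is correct. A reader might infer that a game played at a constantly low score formally passes as achievable. The text does not support that, because its criterion includes the word high and such a game fails it on its face. What stands is narrower: the analysis offered to determine the matter cannot detect the failure.

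A reader might also infer that a small fall from a very high score, such as 98 to 95, would count against a game. It would not. The wording "but not or less so for performance scores" allows for a weaker effect on performance than on level, and 95 may well still be high.

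A third tempting reading is that testing a level set by the therapist is an error. Section 2.7.2 asks whether delivery in the clinical pathway yields a progressive programme, so therapists' prescribing is part of what is studied. A rise in level describes that prescribing. Whether participants coped has to come from performance.

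On size, 15 users per game is pessimistic, since therapists were advised to prescribe all exercises by default. With 70 users the miss rate is 9%, so the second gap is then small under the assumed SD. The first gap does not shrink with sample size.

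Finally, a cut-off per game could sit in the supplement on exercises and metrics or in a fuller plan, neither of which is shown. The absence of a number is therefore not the finding. The article itself fixes the test, the factor and the expected pattern, and these do not address its criterion. Dropouts, adherence and user experience may also reveal excess difficulty, but they do not measure performance.

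**Conclusion.** The point holds in this form: achievable is defined by high, maintained scores, and the analysis named to determine it tests change only. That the test is blind to the height of the scores follows from algebra and rests on no assumption.

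The weakness of non-significance as evidence of maintenance depends on the number of users and on the spread. Under the assumed 25-point SD, a 10-point fall is missed in 70%, 21% or 9% of cases with 15, 50 or 70 users. The score scale, SDs, correlation and users per game are assumptions, as is 5% two-sided here, which the article states only for the TUG sample size.

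This should be changed because it concerns a named feasibility component. It does not affect the TUG comparison, and no stated decision hangs on it.

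**What to change.** Before the data are opened, set two values for each game: a reference score that counts as high, and a margin for tolerable decline. Then:

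- For each part of the programme, report mean performance with its 95% CI against the reference.
- Report the first-to-last change with its 95% CI against the margin. Under the assumed SD of 25, the half-width is t(0.975; n − 1) × 25/√n: 13.8 points with 15 users, 7.1 with 50 and 6.0 with 70. This shows openly when a game has too few users to support a claim.
- Report change in level beside performance at that level, as a description of how therapists progressed the programme.
- Keep the Time ANOVA as descriptive, and state that non-significance will not be read as maintained.

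The change is to analysis wording and uses portal data already collected. The price is that a reference and a margin must be chosen and justified per game in advance, and some games may not qualify as achievable.

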#### Training with Strolll AR intervention independently at home (6 weeks)

2.2.6

The Strolll AR intervention, integrated with usual care, comprises of a 6-week home-based individualized AR gait-and-balance exercise program assisted with tailored AR cues when deemed beneficial. The AR exercises are designed to train aspects associated with gait, balance, and falls risk in a gamified manner to maximize training compliance. Strolll AR comprises seven AR exercises, namely Basketballl, Smash!, Mole Patrolll, Hot Buttons, Puzzle Walk, Wobbly Waiter, and Cue Challenge (Figure 4; see Supplementary material S2 for a detailed description of all AR exercises), intended to improve gait, balance, and falls risk in people with Parkinson’s disease. Exercises that require walking have optional complementary AR cueing (Smash!, Cue Challenge), integrated cueing (speed cue in Wobbly Waiter) or AR-mediated goal-directedness (the moles in Mole Patrolll, the puzzle pieces in Puzzle Walk), to various degrees enabling and assisting people with more severe mobility impairments to participate. For each AR exercise, feedback of performance in terms of game-play performance metrics and functional performance metrics are given during the exercises. For Basketballl, for example, metrics associated with the number of balls thrown in the basket (game-play performance) and the number of sit-to-stands or squats made (functional performance) are given, derived from AR glasses data. See Supplementary material S2 for more details on the AR exercises, metrics, and types of cues.

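### The per-game performance analysis keeps only participants with scores in all three parts, so a game stopped because it was too hard would raise the score level used to call it achievable

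*Protocol article*

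**What the plan says.** Section 2.7.2 of the protocol article asks whether the programme is progressive but achievable, meaning "increasing exercise levels over weeks while maintaining high-performance scores". To test this, "levels and performance scores for each game were subjected to repeated-measures ANOVAs (or their non-parametric equivalent) with the factor Time", where Time has "3 levels, first, middle, last part". Section 2.2.6 likewise defines the second half of the claim by the level of the scores: "achievable (consistently high game-play performance scores) as intended".

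Section 2.2.6 also states that "Strolll AR comprises seven AR exercises". It describes who plays which: "Therapists were by default recommended to prescribe all AR exercises", but "they were allowed to make adjustments, if necessary, to align with" the participant's abilities and needs, and for practical reasons. The therapist sets the exercises, their duration, difficulty and order, and reviews the prescription weekly with the portal's performance metrics in hand.

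The rule for gaps in Section 2.7 is one sentence: "Missing data will be excluded analysis-by-analysis". The article does not say how a game that was never prescribed, or was stopped, counts in the performance result.

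**The concern.** A three-level repeated-measures ANOVA in its standard form, and the Friedman test as its non-parametric counterpart, need a value in every part. Under the stated missing-data rule, a participant whose game was stopped after the first or middle part drops out of that game's analysis, earlier scores included. That participant is still in the trial, so this is a separate route from dropout.

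The exclusion can depend on the outcome being analysed, because the therapist adjusts the prescription using the same performance metrics. A game stopped because it was too hard is evidence about achievability, yet it would leave no trace in the result. Each of the seven games could also be analysed on a different, selected subset.

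Performance is one of the four named aspects of feasibility, which the abstract lists as a primary study parameter. No other planned result fills the gap. Adherence is calculated over prescribed exercises only, so a withdrawn game leaves that denominator too. The safeguard in Section 2.7.2 against looking only at completers covers participant experience and not performance.

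**Working it through.** The article states no figure for this analysis, so there is none to reproduce. It also gives no withdrawal rate and no scores. All values below are assumptions, chosen to show direction and rough size. The cut-offs are illustrative; the plan uses none.

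**Set-up for scenarios A to C.** One game has three normally distributed part scores, SD 15, with equal correlation r of 0.6 or 0.8 between parts. If participants are kept only when one part's score is at or above a cut-off c, that part's mean rises by d = SD × φ(z)/Φ(z), with z = (mean − c)/SD. The means of the other two parts rise by r × d.

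**A. Stable truth: means 75, 75, 75; game stopped when the first-part score is below 60.**
- z = (75 − 60)/15 = 1, so 15.9% are removed.
- d = 15 × 0.2420/0.8413 = 4.31.
- Analysed first-part mean: 75 + 4.31 = 79.3.
- Analysed last-part mean: 75 + 0.6 × 4.31 = 77.6, or 75 + 0.8 × 4.31 = 78.5. The truth is 75.
- Share scoring at least 60 in the last part: 90% to 93%, against 84% for all.
- First-to-last change: −(1 − r) × 4.31 = −1.7 (r = 0.6) or −0.9 (r = 0.8). The truth is 0.

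**B. As A, but only half of the low scorers have the game stopped.**
- Removed: 0.5 × 15.9% = 7.9%.
- First-part mean too high by 15 × 0.2420 × 0.5/0.9207 = 1.97.
- Last-part mean too high by 0.6 × 1.97 = 1.2, or 0.8 × 1.97 = 1.6.

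**C. Falling truth: means 78, 72, 66; game stopped when the middle-part score is below 60.**
- z = (72 − 60)/15 = 0.8, so 21.2% are removed.
- d = 15 × 0.2897/0.7881 = 5.51.
- Analysed last-part mean: 66 + 0.6 × 5.51 = 69.3, or 66 + 0.8 × 5.51 = 70.4. The truth is 66.
- Share scoring at least 60: 75% to 79%, against 66% for all.
- First-to-last change: the first and last parts both rise by r × 5.51, so it stays at −12.0, which is correct.

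**D. Individual slopes differ (simulation, 400,000 draws).** Mean 80 in the first part, falling 3 points per part; between-person SD 10, slope SD 5, residual SD 6. The game is stopped after a first- or middle-part score below the cut-off.

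| Cut-off | Kept | Last-part mean (truth 74.0) | First-to-last fall (truth 6.0) |
|---|---|---|---|
| 60 | 89% | 76.4 | 5.6 |
| 65 | 79% | 78.1 | 5.3 |
| 70 | 65% | 80.4 | 5.1 |

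**Does using all available parts help?** With likelihood-based estimation, the last-part mean is corrected by its regression on the parts that were seen.
- A, r = 0.6: 77.59 − 0.6 × (79.31 − 75) = 75.0.
- C, r = 0.6: the coefficient on each earlier part is 0.6/1.6 = 0.375, and 69.31 − 0.375 × (3.31 + 5.51) = 66.0.
- D: the same approach returned 74.0 at all three cut-offs.

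In these scenarios stopping depends only on scores already recorded, and the correction relies on that.

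**Reading.** The analysed score level is too high in every scenario. The Time contrast is unbiased in C, shows a false decline in A, and understates the true decline in D.

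**The case against.** **The planned test concerns Time.** Section 2.7.2 tests change over the three parts, and that change is not consistently biased towards achievable. In scenario A it is biased against. This stands. A reader might infer that the plan tends to return both progressive and achievable whatever happens. The documents do not support that: the Time contrast can move either way, and exercise levels, on which the progressive half rests, were not examined here. The score level remains affected, and Section 2.2.6 defines achievable by consistently high scores.

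**Withdrawal of games is inferred.** The article never says that a game is dropped for poor scores. A therapist may lower the difficulty instead, which the analysis of levels would show, or leave a game out for practical reasons, which need not bias anything. This stands, and the frequency is unknown. Still, the therapist controls which exercises are prescribed, and playing all seven is only a default.

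**The programme is meant to be tailored.** Changing the mix of games is part of the intervention, so scoring each ability-related withdrawal as a failure would change the question. This largely stands and is why such scoring belongs in a sensitivity analysis.

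**Other results would show problems.** Unsuitability for home use, dropouts with reasons, barriers and the focus group are all reported, but none gives a count per game.

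**An article condenses.** Details of unplayed games could sit in a fuller document. However, the article itself fixes both the ANOVA and the exclusion rule, and together they produce the selection.

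**Conclusion.** The point holds in a limited form. The per-game ANOVA and the exclusion rule together drop anyone without a score in all three parts. Because prescriptions may be adjusted to ability using the same metrics, that loss can depend on the outcome. If it does, the analysed score level is too high: by about 1.2 to 1.6 points with 8% removed, 2.6 to 3.5 with 16% and 3.3 to 4.4 with 21% (scenarios A to C), and by 2.4 to 6.4 points with 11% to 35% removed (scenario D). These sizes rest wholly on assumed scores and withdrawal rules; the documents support a direction and no magnitude. No consistent bias in the Time test and no effect on the progressive claim has been shown. The point concerns one feasibility aspect and leaves the TUG comparison untouched. Minor severity; a cheap improvement.

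**What to change.** 1. Replace the complete-case repeated-measures ANOVA for each game with a linear mixed model for Time that uses every part with data, including the earlier parts of games later stopped.
2. For each game and each part, report from the existing portal records how many home starters were prescribed the game and how many played it, with the reason for omission where one was documented.
3. Limit the progressive-but-achievable statement for each game to those prescribed it, and print that count beside it.
4. Optionally, count ability-related withdrawals as not achieved in a sensitivity analysis.

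The cost is slightly more analysis work and possibly less favourable score levels. The mixed model cannot recover games that were never prescribed, so the counts are needed as well. Recruitment began in May 2024 with the last T2 expected in February 2025, so reasons not already noted may be unobtainable; the counts do not depend on them.
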